**Figure 5. F5:**
[figure not shown]
Sham cervical spinal manipulative therapy (supine drop with forearm assist from 2 angles).

**Figure 6. F6:**
[figure not shown]
Sham thoracic spinal manipulative therapy (prone drop with knee assist).

**Figure 7. F7:**
[figure not shown]
Sham lumbopelvic spinal manipulative therapy (prone drop with knee assist).

Table 1 provides a detailed description of the trial interventions using the Template for Intervention Description and Replication (TIDieR) [21]. Immediately following each session, as well as at the beginning of the second session, blinding will be assessed via a 4-item electronic survey taken with the computer program Jotform. Additionally, within 30 days of the trial’s completion, participants will be informed of their group allocation via email.

**Table 1. T1:** Template for intervention description and replication (TIDieR).

Item	Description
Brief name: provide the name or a phrase that describes the intervention.	Drop table-assisted genuine or sham spinal manipulative therapies (SMTs)
Why: describe any rationale, theory, or goal of the elements essential to the intervention.	Using shams in manual therapy (MT) studies allows for comparison of neurological measures (ie, gait parameters) to expose any definitive effects of therapeutic treatments. Blinding efficacy is fundamental to maintaining the validity of said shams. To date, there are limited manual high velocity, low amplitude (HVLA)–mimicking shams that have been validated in MT research.
What (materials): Describe any physical or informational materials used in the intervention, including those provided to participants or used in intervention delivery or training of intervention providers. Provide information on where the materials can be accessed (eg, online appendix or URL).	—^a^
What (procedures): describe each of the procedures, activities, and/or processes used in the intervention, including any enabling or support activities.	Genuine treatment: only one SMT will be performed in each of the 3 regions assessed (cervical, thoracic, and lumbopelvic). The genuine cervical intervention will be performed in the predetermined location using a supine position and a diversified maneuver. The thoracic spine will be treated in a prone position using a double hypothenar thrust maneuver. This will be done with or without an additional drop in the thoracic region at the discretion of the chiropractor and was based on muscle tone in the region. The lumbopelvic region will receive either a prone drop maneuver with 3-4 drops or a side posture push, depending on clinical findings. Sham treatment: only one sham will be performed in each of the 3 regions assessed (cervical, thoracic, and lumbopelvic). For the sham cervical SMT, the participant will be placed in a supine position on a cervical drop piece with the chiropractor’s forearm under the participant’s neck and contact lateral to the cervical spine. This will only be performed unilaterally over the side with the predetermined restriction in the articular pillars. The thoracic sham and the lumbopelvic sham will be performed with the participant in the prone position. Contact for the thoracic sham will be medial to the medial scapular border, and contact for the lumbopelvic sham will be over the lateral gluteal muscles, opposite to the side of the chiropractor’s stance. The chiropractor will contact close to the predetermined site of intersegmental motion restriction in the spine, but no manual thrust will be directed into the spine. Instead, the chiropractor will apply a downward pressure to the drop piece with their forearm (cervical) or knee (thoracic and lumbopelvic), which will elicit a noise from the table that mimics a genuine drop SMT, as well as induced movement of the participant’s body. Only a single drop will be made in all regions to limit any potential joint motion with the procedure.
Who Provided: for each category of intervention provider (eg, psychologist and nursing assistant), describe their expertise, background, and any specific training given.	Georgia-licensed Doctors of Chiropractic (DCs) with 20+ years of combined experience in the delivery of HVLA SMT and ~3 months of sham protocol training.
How: describe the modes of delivery (eg, face-to-face or by some other mechanism, such as internet or telephone) of the intervention and whether it was provided individually or in a group.	Genuine and sham SMTs will be performed individually and face-to-face.
Where: describe the type(s) of location(s) where the intervention occurred, including any necessary infrastructure or relevant features.	Sessions will take place at the [name] Center for Chiropractic Research (CCR), Life University, Marietta, Georgia, United States.
When and how much: describe the number of times the intervention was delivered and over what period including the number of sessions, their schedule, and their duration, intensity, or dose.	Over the course of a ~1-week period, participants will attend 2 sessions (first ~2 hours, second ~1 hour) scheduled at approximately the same time of day.
Tailoring: if the intervention was planned to be personalized, titrated, or adapted, then describe what, why, when, and how.	Genuine and sham SMTs will be delivered to areas of spinal segmental dysfunction as determined by the chiropractic clinician using an established, reliable detection protocol.
Modifications: if the intervention was modified during the study, describe the changes (what, why, when, and how).	—
How well (planned): if intervention adherence or fidelity was assessed, describe how and by whom, and if any strategies were used to maintain or improve fidelity, describe them.	Participant adherence to the intervention schedule will be monitored by the chiropractic clinician. Attempts will be made to mitigate adherence issues via automated SMS text messaging reminders sent ~24 and ~3 hours prior to each session.
How well (actual): if intervention adherence or fidelity was assessed, describe the extent to which the intervention was delivered as planned.	—

a Not applicable.

### Criteria for Discontinuing or Modifying Allocated Interventions

Participants will be advised that they are able to withdraw at any time without giving a reason or may be withdrawn by the investigators if they experience significant adverse effects that are deemed detrimental to their well-being, as determined by the clinician.

### Strategies to Improve Adherence to Interventions

We will attempt to mitigate adherence issues via automated SMS text messaging reminders sent ~24 hours and ~3 hours prior to each session.

### Plans to Promote Participant Retention and Complete Follow-Up

Once enrolled, every reasonable effort will be made to follow participants throughout the entirety of the study period via ongoing email and SMS text messaging correspondence. In the event of premature discontinuation of the study for any reason, participants will be made aware that all data collected up to the point of withdrawal may be used for analyses, though they will have the right to pull their data if so desired.

### Relevant Concomitant Care Permitted or Prohibited During the Trial

Participants will be asked to avoid any outside manual therapies (eg, chiropractic and osteopathy) from 14 days prior to their initial session until the end of the trial period. Any introduction of manual therapies during this period will render participants ineligible.

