### Participant Timeline

This trial will require 2 sessions, one week apart. The participants will receive the same intervention (ie, genuine or sham SMT) at both sessions. The study flow is outlined in Figure 1.

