### Implementation (Enrollment and Assignment)

The clinicians (MS and AJ) are responsible for participant enrollment. Following the initial chiropractic exam and immediately prior to the delivery of the participant’s first sham or real SMT, the participant will be permitted to choose their own envelope from a box, though MS or AJ will be the one to open the envelope to review the group assignment. This assignment will be recorded by MS or AJ in a binder that will only be accessible to her throughout the course of the trial.

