### Measurements (All Assessments Will Be Performed by the Data Team)

#### Primary Outcome

Blinding will be assessed immediately following each session and directly prior to the second session via a brief electronic survey whereby participants will be asked (1) their perceived group allocation (“genuine adjustments,” “sham adjustments,” and “I don’t know”), (2) if their group assignment was revealed to them in any way (“No,” “Yes - explain”), (3) if they felt any changes in their body following their sessions (“No,” “Yes-explain,” and “I don’t know”), and (4) if they have received chiropractic care prior to this study (“No” and “Yes-for how long-what kind”). This data will be stored in Jotform. The Bang BI is a continuous value from −1 to 1 computed on each trial arm [22]. Per the index developers, an index score of 1 indicates that all responses are correct, suggesting complete unblinding. An index of −1 denotes that all responses are incorrect, suggesting either complete blinding or unblinding in the opposite direction if participants have some bias leading them to believe they are in the opposite arm. An index of 0 indicates half of the responses are correct and half are incorrect, which suggests random guessing. Arm-level Bang BIs between −0.3 and 0.3 are commonly interpreted as “successful blinding” [14-16]. Successful blinding might also be inferred in cases of “wishful thinking,” whereby trial participants tend to believe they received genuine treatment irrespective of group assignment, resulting in Bang BIs for the genuine and sham groups approaching 1 and −1, respectively (summed Bang BI ≈0) [23].

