### Methods in Analysis to Handle Protocol Nonadherence and Any Statistical Methods to Handle Missing Data

We will report the number and percentages of withdrawals in each of the groups. Based on the trialists’ experience, loss to follow-up is expected to be no more than 15%, which has been factored into our sample size calculation. Regarding secondary outcomes, mixed models have been shown to provide robust estimates in longitudinal designs even with high levels of missing data.

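### The ban on outside manual therapy is worded as an eligibility rule that runs past randomisation, so it can remove randomised participants for a reason plausibly related to the primary outcome

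*Protocol article*

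**What the plan says.** The section on concomitant care asks participants to avoid outside manual therapies "from 14 days prior to their initial session until the end of the trial period" and continues: "Any introduction of manual therapies during this period will render participants ineligible".

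Under Implementation (Enrollment and Assignment), the envelope is drawn after the initial examination and "immediately prior to the delivery of the participant’s first sham or real SMT". Participant Timeline adds: "This trial will require 2 sessions, one week apart". About one week of the restricted window therefore falls after allocation.

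Under Primary Outcome, "Blinding will be assessed immediately following each session and directly prior to the second session". The item that feeds the index is "their perceived group allocation". On interpretation: "Arm-level Bang BIs between −0.3 and 0.3 are commonly interpreted as" successful blinding.

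On what happens to the data:

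- The retention section permits, but does not require, use of data gathered before a withdrawal, and lets participants pull their data. It does not mention people ruled ineligible.
- The discontinuation section covers participant choice and significant adverse effects, not outside care.
- The nonadherence and missing-data section says "We will report the number and percentages of withdrawals in each of the groups", restates the 15% loss allowance, and for secondary outcomes relies on mixed models. It gives no rule for the Bang BI.

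**The concern.** Eligibility decides who may enter a trial. Here the same label is attached to something a participant does after being randomised and treated. The Eligibility Criteria already require two weeks without chiropractic care before participation, so for chiropractic the main thing this rule adds is its reach past allocation.

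That matters more here than in most trials because the outcome is a belief. Someone who suspects a sham, or who felt nothing change, may have more reason to seek care elsewhere before session 2. If that person is then left out, the analysis set has been selected on something related to the guess itself. In the sham arm the person would be a correct guesser, and in the genuine arm an incorrect one. The visit-2 gait comparison would also no longer be between the groups as randomised.

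**Working it through.** **Does the rule reach randomised participants?** Yes. The window opens 14 days before session 1 and closes at the end of the trial period. Allocation is at session 1 and session 2 is one week later. Taking the trial period to be the participant's own, the post-allocation part is about one week.

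**Which measurements are exposed?**

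| Measurement | Can outside care after allocation come before it? | Consequence of the rule |
|---|---|---|
| Blinding survey after session 1 | No | Affected only if all of the participant's data are discarded |
| Blinding survey before session 2 | Yes | Directly exposed |
| Blinding survey after session 2 | Yes | Directly exposed |
| Gait at end of session 2 | Yes | Directly exposed |

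**Arm size.** The Sample Size section starts from 25 per arm and allows 15% loss: 25/(1 − 0.15) = 29.4, rounded up to 30. The plan's figure reproduces, and 30 is used below.

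**Effect of losing a participant on the Bang BI.** In an arm with c correct guesses, i incorrect guesses and n participants, B = (c − i)/n. "Don't know" answers count only in n.

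- Losing k correct guessers gives (c − i − k)/(n − k). The first such loss changes B by −(1 − B)/(n − 1).
- Losing k incorrect guessers gives (c − i + k)/(n − k). The first such loss changes B by +(1 + B)/(n − 1).
- Loss unrelated to the guess leaves B unchanged in expectation.

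**Illustration.** The answer splits (correct/incorrect/don't know) are assumed; the documents give none.

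| Sham arm, n = 30 | All kept | Correct guessers lost | Result |
|---|---|---|---|
| 18/8/4 | 10/30 = 0.333 | 1 | 9/29 = 0.310 |
| 18/8/4 | 0.333 | 2 | 8/28 = 0.286 |
| 14/10/6 | 4/30 = 0.133 | 3 | 1/27 = 0.037 |
| 18/6/6 | 12/30 = 0.400 | 4 | 8/26 = 0.308 |
| 18/6/6 | 0.400 | 5 | 7/25 = 0.280 |
| 12/12/6 | 0/30 = 0.000 | 5 | −5/25 = −0.200 |

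The change per person is about 0.02 (18/6/6: 0.120/5 = 0.024) to 0.04 (12/12/6: 0.200/5 = 0.040). The 18/8/4 split falls below 0.3 after two losses. The 18/6/6 split needs five, which is 5/30 = 17% of the arm.

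**The other arm.** In a genuine arm with 18/6/6, losing two incorrect guessers moves B from 0.400 to (18 − 4)/28 = 0.500, further from the success band.

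**The case against.** **The rule does not say that data are deleted.** This stands in part. The article says ineligible, not excluded from analysis, and it permits use of data gathered before a withdrawal. The survey after session 1 need not be lost. But that permission is optional, is written for withdrawals, and does not help at visit 2. A literal reading of the rule still allows the participant to be dropped.

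**Analysis sets belong in the statistical analysis plan.** True in general, and their absence here would be no finding. The point is that a sentence actually written applies eligibility after allocation.

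**The link between belief and outside care is conjecture.** This stands. The documents neither state nor quantify it and give no rate of outside care. The window is about a week, in healthy adults asked to avoid such care, so numbers may be small. On the other side, Strengths and Limitations describes the local population as more familiar with chiropractic, and regular users can enrol after a two-week gap.

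**The verdict would not really turn on this.** A reader might infer that the rule biases the sham arm towards apparent success and that two exclusions reverse the conclusion. The documents do not support that. The two-loss case starts just above the limit; the 18/6/6 case needs 17% of the arm lost, all correct guessers, against at most 15% loss expected from all causes. The ±0.3 band is a common interpretation, not a planned pass/fail test, and the change from 0.333 to 0.286 is small beside the planned interval width of 0.45.

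**Outside manipulation contaminates visit-2 data.** Also fair. It could alter gait directly and give the participant a fresh comparator for the guess. That supports an additional analysis without these participants, but not their silent removal from the main one.

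**Conclusion.** The concern holds in a limited form. An eligibility rule is applied to behaviour after randomisation, and the article does not commit to analysing the affected participants in their assigned arm. Followed literally, it permits an exclusion plausibly related to perceived allocation, which is the primary outcome.

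Direction and size cannot be determined from the documents. The shift of about 0.02 to 0.04 per correct guesser lost rests on assumed answers, an arm of 30, and the assumption that everyone lost guessed correctly. Loss of incorrect guessers from the genuine arm would raise that arm's index instead. It would also go too far to say that the gait comparison is broken: gait is exploratory, reported by estimation only, and compromised only to the extent that such exclusions occur. The point deserves correction because the remedy is simple, not because a large bias has been shown.

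**What to change.** Change the analysis side only:

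1. State that, for analysis purposes, ineligibility because of outside manual therapy applies only before allocation.
2. Record any outside manual therapy after allocation as a protocol deviation, by arm.
3. Keep every randomised participant who has available data, and has not withdrawn those data, in the assigned arm for the Bang BI, James BI and gait analyses.
4. Repeat those analyses without the participants who had outside care, as a sensitivity analysis.

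The request to avoid outside care, and whether such a participant goes on to session 2, are clinical and conduct matters not judged here. Where visit-2 data were never collected, this change cannot supply them.

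The cost is a sentence or two in the protocol, with no change to sample size or data collection. With 25 participants enrolled by February 11, 2026 against a target of 60, the rule can be settled well before analysis. The downside is that a few participants with outside care remain in the main visit-2 blinding estimates and the exploratory gait estimates; the sensitivity analysis shows how much they matter.

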### Measurements (All Assessments Will Be Performed by the Data Team)

#### Primary Outcome

Blinding will be assessed immediately following each session and directly prior to the second session via a brief electronic survey whereby participants will be asked (1) their perceived group allocation (“genuine adjustments,” “sham adjustments,” and “I don’t know”), (2) if their group assignment was revealed to them in any way (“No,” “Yes - explain”), (3) if they felt any changes in their body following their sessions (“No,” “Yes-explain,” and “I don’t know”), and (4) if they have received chiropractic care prior to this study (“No” and “Yes-for how long-what kind”). This data will be stored in Jotform. The Bang BI is a continuous value from −1 to 1 computed on each trial arm [22]. Per the index developers, an index score of 1 indicates that all responses are correct, suggesting complete unblinding. An index of −1 denotes that all responses are incorrect, suggesting either complete blinding or unblinding in the opposite direction if participants have some bias leading them to believe they are in the opposite arm. An index of 0 indicates half of the responses are correct and half are incorrect, which suggests random guessing. Arm-level Bang BIs between −0.3 and 0.3 are commonly interpreted as “successful blinding” [14-16]. Successful blinding might also be inferred in cases of “wishful thinking,” whereby trial participants tend to believe they received genuine treatment irrespective of group assignment, resulting in Bang BIs for the genuine and sham groups approaching 1 and −1, respectively (summed Bang BI ≈0) [23].

#### Secondary Outcomes

##### James BI

The James BI will also be used for evaluating the blinding success of the participants based on their electronic survey answers as noted above. The James BI is calculated based on the proportion of participants who correctly or incorrectly guess their treatment group, where a “don’t know” response is considered a successful blinding outcome [22]. This index is scored on a scale of 0-1; a score of 0 indicates complete lack of blinding, while a value of 1 indicates perfect blinding. Generally, acceptable blinding is indicated when values are between 0.5 and 1 [13].

##### Gait

Secondary outcomes will assess the effects of spinal manipulative therapy on spatiotemporal gait characteristics. Gait will be evaluated using inertial measurement motion capture units and an instrumented force-plate treadmill (Noraxon USA Inc). Spatiotemporal gait parameters will include step length, step time, cadence, and velocity. Gait events will be identified using vertical ground reaction force thresholds implemented within Noraxon’s analytical pipeline. Where applicable, parameters will be processed bilaterally and averaged to generate representative values for each participant. Gait will be evaluated at baseline and at the end of the second session to assess changes over time, as well as differences between participants receiving genuine SMT versus sham SMT.

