Two widely referenced tools in manual therapy studies are the Bang Blinding Index (Bang BI) and the James Blinding Index (James BI), which offer distinct approaches to accurately measuring blinding [13,14]. The Bang BI examines blinding separately for each treatment group and evaluates both the degree and direction of potential bias. In contrast, the James BI provides an overall interpretation of blinding by comparing correct guesses to what would be expected by chance, where “don’t know” responses are regarded as optimal [13,14]. As such, the Bang BI helps with the identification of group-specific bias patterns, whereas the James BI provides a more overall view of blinding success [13-15]. When used together, these 2 indices can strengthen confidence in a study’s internal validity by offering complementary interpretations of the results. Recent studies have evaluated the use of these 2 indices and recognized the feasibility, utility, and importance of them in manual therapy trials [15,16]. These studies also highlighted the importance of testing blinding in manual therapy research, especially in chiropractic trials where tactile and treatment context cues may influence participants’ expectations. Blinding efficacy is fundamental to maintaining the validity of clinical trials, especially when comparing the differences between sham and genuine SMTs.

In addition to blinding efficacy, we are also interested in exploring the possible neurophysiological mechanisms potentially responsive to change following chiropractic care. It is therefore relevant to quantify and assess movement-related measures such as gait parameters to elucidate the definitive effects of such therapeutic treatments. Contemporary evidence involving genuine SMTs has provided evidence to suggest such therapies result in improvements in several gait parameters, including step length and gait symmetry [17]. However, there is limited data comparing gait outcomes between genuine SMTs and shams. Therefore, we aim to expand the literature on the potential impacts of SMT on movement-related outcomes within the context of a putatively robust study design.

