### Assessments

Participants will be asked to attend 2 separate sessions approximately one week apart. Automated text reminders will also be sent via ChiroHD software (ChiroHD Inc) ~24 hours and~3 hours prior to each session.

To assess gait, participants will be asked to walk on a motorized treadmill at their preferred walking speed (PWS). Participants will be fitted with 16 inertial measurement units at different anatomical landmarks. Inertial measurement units will then be calibrated using commercial motion-capture equipment (NORAXON MyoMotion, MR2; Noraxon Inc). Participants will be fitted with a pair of slip-resistant socks prior to testing. They will then be instructed to step onto the nonmoving treadmill to begin the PWS assessment. Participants will start by walking on the treadmill at a speed of 0.5 mph. A trained research investigator will then increase the speed by 0.1 mph increments every 2‐4 seconds until the participant reports that they are walking at their PWS. Then, in 0.1 mph increments, 1 mph is added to the speed, followed by a decrease at a rate of 0.1 mph every 2‐4 sec until they re-establish their PWS. This procedure will be repeated 3 times in total. The speeds will be averaged to determine their PWS. The PWS assessment will only be performed at baseline. Participants will also be blinded to the digital speed display while walking on the treadmill. Once the PWS has been established, participants will be asked to walk on the treadmill for 5 minutes at their PWS. The treadmill will be used to measure forces during walking, as well as several traditional gait parameters (eg, step time, stride time, and steps per minute in milliseconds). Gait assessment during the follow-up session will be identical, except for determining PWS.

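### Velocity is listed as a gait outcome, but the treadmill runs at the baseline speed at both visits, so velocity cannot respond to treatment and the other three listed averages are near-duplicates

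*Protocol article*

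**What the plan says.** The Gait section under Secondary Outcomes names four parameters: "Spatiotemporal gait parameters will include step length, step time, cadence, and velocity". It places the measurements at baseline and at the end of the second session, and gives the purpose as change over time and genuine-versus-sham differences. Where applicable, left and right sides are combined: "parameters will be processed bilaterally and averaged to generate representative values for each participant".

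The Assessments section describes how the walk is done. The surface is a motorized treadmill. Preferred walking speed (PWS) is found by raising and lowering the belt speed, three times in total: "The speeds will be averaged to determine their PWS". The measured walk follows: "participants will be asked to walk on the treadmill for 5 minutes at their PWS". On timing it says "The PWS assessment will only be performed at baseline", and on the second visit "Gait assessment during the follow-up session will be identical, except for determining PWS".

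Statistical Considerations (Secondary Outcomes) models each gait outcome as change from baseline in a linear mixed model with that outcome's own baseline, age and sex as covariates. A gamma model with log link is the fallback. The section promises estimation without significance testing, notes that the gait measures are correlated, and applies a Bonferroni correction without stating the number of comparisons.

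**The concern.** An outcome analysed for change has to be free to change. The motor imposes the walking speed, that speed is chosen before treatment, and the same speed is used again after treatment. Velocity is then a setting of the test and not a response to it. A between-arm difference close to zero with a very narrow interval is assured whatever spinal manipulation does, and it could easily be reported as evidence that manipulation leaves walking speed unchanged.

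Fixing the speed also ties the remaining three averages together. If step length, step time and cadence all move in compatible directions, the result will look like three supporting findings when it is close to one finding in three units.

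**Working it through.** The protocol gives no power or precision figure for gait, so there is none to reproduce. The check is whether the stated procedure lets the stated outcomes vary.

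**1. Belt speed at the two walks.** Baseline walk: 5 minutes at PWS. Follow-up walk: the same assessment without determining PWS. The only PWS available at follow-up is the baseline value, so v(follow-up) = v(baseline). No section describes a self-paced belt, an overground walk or a second PWS determination.

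**2. Velocity change.** Measured mean velocity is (belt distance + net drift along the belt) / time. With no drift, the change is v − v = 0. Assume net drift of at most ±0.2 m per walk. Two 300-second walks can then differ by at most 0.4/300 = 0.0013 m/s. A simulation of 60 walkers, with assumed mean speed of about 1.1 m/s, step time of about 0.55 s and that drift, gave an SD of velocity change of 0.0005 m/s and a maximum of 0.0011 m/s on a mean speed of 1.09 m/s. The change score carries only noise. The fallback model does not help, because a gamma distribution cannot be fitted to zero or negative changes.

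**3. The other three averages.** At constant v and mean step time T:
- mean step length = v × T
- cadence = 60 / T
- velocity = step length × cadence / 60 = v

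Illustration with assumed v = 1.1 m/s:

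| | T (s) | step length (m) | cadence (steps/min) | velocity (m/s) |
|---|---|---|---|---|
| Baseline | 0.550 | 0.605 | 109.1 | 1.1 |
| T longer by 2% | 0.561 | 0.617 | 107.0 | 1.1 |

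Step length rises by the same 2%, cadence falls by the reciprocal factor (1/1.02), and velocity does not move.

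**4. The scale that will be analysed.** The planned model uses raw change. Raw step-length change is v × (change in T), and v differs between participants: a 0.011 s change in T is 0.0121 m at 1.1 m/s but 0.0138 m at 1.25 m/s. In the simulation, absolute correlations between the three changes were at least 0.9998 on the log scale and 0.986 to 0.994 on the raw scale. They are near-duplicates, not identical numbers.

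**5. Multiplicity.** Assume that the correction is applied to the intervals. The two-sided 5% normal multipliers are:

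| Parameters counted | z | Ratio to 1.960 |
|---|---|---|
| 1 | 1.960 | 1.00 |
| 2 | 2.241 | 1.14 |
| 3 | 2.394 | 1.22 |
| 4 | 2.498 | 1.27 |

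Going from four to two parameters changes the multiplier by 2.498/2.241 = 1.11.

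**The case against.** Several points on the other side are fair.

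- **Gait is secondary and exploratory.** This stands. The Bang index analysis and the sample size do not depend on gait. But caution in interpretation does not help an outcome that cannot respond at all.
- **The list is open-ended.** The Gait section says what the parameters will include, and the Assessments section also mentions forces and stride time. The redundancy therefore applies to the four named averages, not to everything that the equipment records.
- **Correlation is already acknowledged.** The statistical section says that the gait measures are correlated. It does not say that one is fixed by the test and that the rest follow from one another.
- **A condensed article may leave detail elsewhere.** The point is not an omission. Two sections state an outcome and a procedure that are incompatible, and an analysis plan cannot restore variation that the measurement has removed.

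Stronger readings are tempting but not supported. A reader might infer that the four outcomes are exactly one quantity; on the raw change scale of the planned model that is only approximately so. A reader might infer that every interval will be 27% too wide. That figure compares four parameters with one, while the protocol states neither the number of comparisons nor that its 95% intervals will be widened. A reader might also infer that averaging the sides defeats a symmetry question that the trial poses. The Introduction only cites earlier evidence of "improvements in several gait parameters, including step length and gait symmetry", as examples; the stated aims do not include symmetry, and averaging is qualified as applying where applicable.

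**Conclusion.** The velocity outcome is wrong as written. Under the stated procedure its expected change is zero in both arms for any true treatment effect, with only drift and sensor noise left, so the planned model cannot estimate a treatment effect on it. This assumes that the follow-up belt is set to the baseline PWS, which is the natural reading of the Assessments section. The noise figures depend on assumed speed, step time and drift; the zero does not.

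Step length, step time and cadence can still respond to treatment at a fixed speed, so the gait aim is not defeated. Their agreement, however, is not independent corroboration. The effect on multiplicity depends on an unstated number of comparisons: a multiplier of 2.498 if all four are counted, against 1.960 for one or 2.241 for two. The primary blinding result is unaffected. This should be corrected, but it does not threaten the trial's main conclusion.

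**What to change.** - Remove velocity from the gait outcomes and from the Bonferroni family. Report belt speed by arm as a baseline descriptor, so that the Gait and Assessments sections agree.
- Name one of step length, step time or cadence as the averaged gait endpoint. Present the other two as re-expressions of it, without counting them separately in the correction.
- State how many parameters the Bonferroni correction covers and whether it is applied to the intervals.

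Optional, and not the correction of an error: a left-right asymmetry measure could be derived from the same recordings before the sides are averaged, since the Introduction cites symmetry among the parameters reported to improve. With one averaged endpoint, that would make two parameters.

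The cost is a shorter outcome list and a documented protocol amendment. No visit, recording or intervention changes, so the revision can apply to all participants, including the 25 reported as enrolled by February 11, 2026.
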